**Trial registration number:**

Main sponsor: Imperial College London, Reference: 19QC5491. Funders: NIHR HTA, Reference: 127 976. Study coordination centre: Imperial College Healthcare NHS Trust, [name] with Centre for Trials Research, College of Biomedical & Life Sciences, Cardiff University. IRAS Project ID: 266 400. REC reference: 20/LO/0031. ISRCTN registry: 76 016 200.

Strengths and limitations of this studyChanges in cerebral Doppler measures are considered a strong candidate for triggering delivery following detection of late preterm fetal growth restriction.The primary outcome is a composite of perinatal and neonatal outcome, and infants will be followed to determine health and neurodevelopment at 2 years to ensure safety and non-inferiority of intervention.This appropriately powered UK and European multicentre trial will inform NHS policy and the findings will be generalisable to late preterm fetal growth restriction in other healthcare systems.There are limited data available in respect of selecting the threshold of cerebral Doppler change for randomisation.Some non-UK centres will not randomise women at the earlier gestation range (32–33+6 weeks) and this could limit the generalisability of the results in this group of women.

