We then carried out the prospective multicentre observational TRUFFLE 2 Feasibility Study (2017–2018, n=1024). A range of markers of cerebral redistribution were evaluated as potential delivery trigger points in two gestational age bands. These included the MCA Doppler and the umbilical cerebral ratio (UCR); calculated by dividing the Doppler pulsatility index of the umbilical artery by that of the MCA. Participating clinicians suggested greater concern about fetal condition is required to trigger delivery at earlier rather than later gestational ages between 32 and 36 weeks. We, therefore, selected a more abnormal threshold for cerebral redistribution at earlier gestational ages, based on stepped UCR z-score values.^16^ Of note was the finding from a prospective study that birth condition, fetal mortality and neonatal morbidity rate were more common among fetuses showing higher UCR z-score, indicating cerebral redistribution, compared with those with a lower UCR z-score (15 vs 9%).^17^

On this basis, we designed this randomised trial of delivery for women identified with late preterm FGR, to test the hypothesis that delivery based on UCR values derived from the feasibility study will safely lead to improved fetal outcomes (TRUFFLE 2).

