#### Eligible for randomisation: consent for randomisation

Consent for randomisation once cerebral redistribution is identified, with UCR (as defined above) of ≥1.0 at 32+0 to 33+6 weeks and ≥0.8 at 34+0 to 36+6 weeks. This consent will also include contact details and willingness to be contacted in the future for follow-up data collection (online supplemental file 3—consent for randomisation).

10.1136/bmjopen-2021-055543.supp3Supplementary data

Women are randomly allocated to either immediate delivery or delayed delivery as defined below. Randomisation has a 1:1 allocation ratio and stratified based on gestational age (above or below 34 weeks) and centre. Randomisation is conducted on the electronic data capture platform (Castor EDC, Amsterdam, The Netherlands).

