### Statistics and data analysis

#### Sample size

The trial is powered to detect if immediate delivery following cerebral redistribution is superior to expectant management following cerebral redistribution on this outcome. A difference in the proportion with the primary outcome from 15% in the delayed delivery to 9% in the immediate delivery (from TRUFFLE 2 feasibility study) demonstrates an OR of 0.56. At two-sided 5% significance with 95% power, 780 participants per arm are required, giving 1560 in total. Given the immediacy of this outcome, no loss to follow-up is expected. An important non-inferiority secondary safety outcome is infant neurodevelopment, which is measured by parent completed questionnaire at 2 years using the PARCA-R, as recommended in NICE Guidance,^21^ supplemented by infant health information over the intervening 2 years. Assuming a loss to follow-up at 2 years of 20%, 2-year outcomes for approximately 1248 infants are expected (624 per group assuming no difference in the lost to follow-up between the groups). The PARCA-R questionnaire provides a composite score for neurodevelopment with a standardised mean of 100 and SD of 15. With a one-sided significance level of 1%, under a non-inferiority hypothesis, a sample size of 624 in each group achieves a 98% power to detect a non-inferiority margin of difference in the mean PARCA-R score of no less than four points (0.25 of a SD). A margin of no less than three points can be detected with 90% power.

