#### Main analysis

The primary analysis approach for the primary outcome of composite of adverse fetal/neonatal outcomes, maternal secondary outcomes and the Infant Health Questionnaire will be intention to treat with participants analysed in the groups to which they are assigned regardless of deviation from the protocol or intervention received. The PARCA-R will be both an intention to treat and a per protocol analysis, since the hypothesis under examination for these outcomes is a non-inferiority hypothesis. The per-protocol analysis will exclude babies of women who do not receive their intervention as planned. As the trial includes multiple centres (and will involve a reasonable number of participants randomised per centre), the analysis will be based on the individual participant, allowing for clustering between participants within centre using robust SEs. All analyses will additionally adjust for gestational age at inclusion (stratification risk factor used in randomisation) as a fixed factor. For binary outcomes (composite of adverse fetal/neonatal outcomes, gestational hypertension, pre-eclampsia) a logistic regression model will be used to compare this outcome by arm and results presented as ORs and two-sided 95% CI. Continuous outcomes (PARCA-R, Infant Health Questionnaire) will be analysed using linear regression and results presented as adjusted differences in means alongside 95% CIs. The Infant Health Questionnaire will also be examined over time using a repeated measures model, and will include an interaction term for time (6, 12, 18 and 24 months) and trial arm to investigate any divergent or convergent pattern in Infant Health Questionnaire. The categorical outcomes of mode of delivery and onset of labour will be compared between trial arms by fitting a multilevel ordinal regression model. The neonatal secondary outcome will be examined using the mean PARCA-R score between each trial arm using linear regression, and a one-sided 95% CI constructed to assess non-inferiority. Additional pre-specified sub-group analyses will be carried out to analyse the primary outcome in the whole cohort by those that are <10th percentile (vs ≥10th) and <3rd percentile (vs ≥3rd) based on different growth charts, maternal morbidity (yes/no) and corticosteroid administration (yes/no).^22 23^ If numbers are sufficient, we will also describe the intervention effect in the subgroups <3rd percentile versus 4–10th vs >10th percentile but will not statistically test for intervention effect.

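### The qualifying UCR, the trial's own trigger, is neither a covariate in the primary model nor among the named subgroups, so some precision is given up and any UCR analysis would be post hoc as the article stands

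*Protocol article*

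**What the plan says.** Under Eligible for randomisation, allocation is described thus: "Randomisation has a 1:1 allocation ratio and stratified based on gestational age (above or below 34 weeks) and centre". UCR is not a stratifier.

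Under Main analysis, the adjustment set is stated: "All analyses will additionally adjust for gestational age at inclusion (stratification risk factor used in randomisation) as a fixed factor". Centre is handled by robust standard errors. The subgroup list begins "Additional pre-specified sub-group analyses will be carried out to analyse the primary outcome in the whole cohort by those that are <10th percentile" and goes on to the 3rd percentile, maternal morbidity and corticosteroid administration. UCR is not mentioned in that section.

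Elsewhere the article gives UCR a central place:

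- Study design and Inclusion criteria make a repeated UCR of at least 1.0 (32+0 to 33+6 weeks) or at least 0.8 (34+0 to 36+6 weeks) the condition for randomisation. The matching z-score cut-offs are >1.5 and >1.0.
- Study design says that eligibility data are entered on the randomisation platform.
- The Introduction reports that poor outcome was commoner with a higher UCR z-score, "indicating cerebral redistribution, compared with those with a lower UCR z-score (15 vs 9" per cent).
- The strengths and limitations list concedes: "There are limited data available in respect of selecting the threshold of cerebral Doppler change for randomisation".

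**The concern.** The trial tests a policy of delivering once UCR crosses a threshold. The primary odds ratio averages over all women at or above it, from those just over the line to those far beyond. The authors say the threshold was chosen on limited data, so a natural follow-up question is whether the effect differs with the degree of abnormality. The section that names the pre-specified subgroups does not include this one. If it is first examined after an unblinded trial has reported, it will carry the weight of a post hoc analysis.

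There is also a smaller matter of efficiency. A baseline value that is plausibly prognostic, and held for every randomised woman, is not used in the primary model.

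**Working it through.** **1. The planned figure.** Inputs from Sample size: 15% against 9%, two-sided 5%, 95% power, 780 per arm, no loss to follow-up for this outcome.

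n per arm = [1.960·√(2·0.12·0.88) + 1.645·√(0.15·0.85 + 0.09·0.91)]² / 0.06² = (0.9007 + 0.7527)² / 0.0036 ≈ 760, or 793 with continuity correction. The stated 780 lies between them. Power at 780 per arm is 95.5%. OR = (0.09/0.91)/(0.15/0.85) = 0.56, as stated. The sample size is not affected by this point.

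**2. Standard error of the main effect.**

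SE(log OR) = √[1/(780·0.15·0.85) + 1/(780·0.09·0.91)] = √(0.01006 + 0.01565) = 0.160.

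**3. Interaction with UCR as a continuous modifier.** For a modifier scaled to SD 1, the interaction SE per SD is close to the main-effect SE, 0.160. Power = Φ(|ln r|/SE − 1.96), where r is the ratio of treatment ORs per SD of UCR.

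| r per SD | abs(ln r) | abs(ln r)/0.160 | Power |
|---|---|---|---|
| 0.61 | 0.494 | 3.08 | 87% |
| 0.74 | 0.301 | 1.88 | 47% |

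The ratio detectable with 80% power is exp[−(1.96 + 0.842)·0.160] = 0.64 per SD.

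**4. Interaction with UCR split at the median.** Each half has 390 per arm, so the interaction SE doubles to 0.321. For a ratio as large as the main effect (0.56), |ln r| = 0.579 and power = Φ(0.579/0.321 − 1.96) = 44%. The ratio detectable with 80% power is 0.41. Dichotomising is therefore clearly worse than keeping UCR continuous.

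**5. Simulation check.** Settings: 1,560 women, UCR excess over the cut-off exponential and standardised, control rate 15%, treatment OR 0.56 at the mean excess, prognostic OR per SD of 1.28, 1.65 or 2.1.

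- Information gained by adjusting for UCR, taken as (mean adjusted z / mean unadjusted z)² with no interaction: about 1%, 5% and 12% to 13%. The z ratio is used because covariate adjustment in a logistic model moves the log OR as well as its SE.
- Interaction SE: 0.13 to 0.18 per SD.
- Interaction power: 47% to 58% at r = 0.74, and 84% to 95% at r = 0.61. The lower ends belong to the weakest prognostic strength.

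**6. What those ratios mean.** Under the assumed exponential, the cut-off itself lies 1 SD below the mean excess. With r = 0.61, the treatment OR is 0.56/0.61 = 0.92 at the cut-off and 0.56·0.61 = 0.34 at 1 SD above the mean. With r = 0.74 the values are 0.76 and 0.41. The well-powered case thus requires almost no effect at the threshold.

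**7. Scale.** The z-score cut-off is >1.5 in the early band and >1.0 in the later one, so the early band holds no values from 1.0 to 1.5. A raw z-score interaction would partly measure gestational band.

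**The case against.** The strongest reply is that this is ordinary SAP content. The article defers detail to an SAP that is not shown and may already include a UCR term. That limits the claim: it concerns what the article fixes, not what the trial will finally do. It does not remove the point, because the article does not leave these items open. It states the adjustment set and names the pre-specified subgroups, and the trigger variable is absent from both.

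Other parts of the reply stand in full, and they rule out stronger readings that a reader might infer:

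- **That the trial cannot say whether benefit depends on UCR.** Eligibility data are recorded, so the analysis remains possible. What is missing is pre-specification.
- **That the article shows risk rising with UCR among randomised women.** The Introduction gives one contrast between higher and lower z-scores. It shows no gradient above the cut-off, and only women at or above it are randomised.
- **That the analysis would settle where the threshold belongs.** Women below the cut-offs are not randomised, so nothing can be learned about looser thresholds. The stated limitation concerns how the threshold was selected. It does not claim that benefit varies above it.
- **That the primary result is biased or answers the wrong question.** Leaving out a baseline covariate does not bias a randomised comparison, and the pooled OR is the right estimate for a policy at a defined trigger.

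The precision gain is also small beside a design with about 95% power.

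**Conclusion.** The point holds as an inexpensive improvement, not as an error in the primary analysis. The article fixes its covariates and names its subgroups without the variable that triggers randomisation.

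The cost of the omission is about 1% to 13% of information on the primary comparison, assuming no interaction and a prognostic OR of 1.28 to 2.1 per SD within the randomised range. It also means that, on the article's text, any treatment-by-UCR result would be post hoc. A pre-specified interaction would have about 50% power for a ratio of 0.74 per SD and about 85% or more only for a strong ratio of 0.61, so it can only be exploratory.

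The UCR distribution, its prognostic strength above the cut-off and the interaction sizes are all assumptions, since the article gives none of them.

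**What to change.** Amend Main analysis, and carry the change into the SAP before database lock:

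1. Add the qualifying UCR at randomisation, as a continuous z-score, as a covariate in the primary logistic model alongside gestational age.
2. Pre-specify one exploratory treatment-by-UCR interaction on the primary outcome. Keep UCR continuous and express it as excess over the gestational-band cut-off, or fit it within band with a treatment-by-gestational-band term. Report the treatment OR with 95% CI across the observed UCR range.
3. State that this analysis can inform stricter thresholds only, not looser ones.

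The cost is wording. No new data and no change to the sample size are needed. The drawbacks are modest power for the interaction and a primary OR that becomes conditional on UCR, which should be said when it is reported.

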## Methods and analysis

### Study design

This is an individual unblinded randomised trial of pregnant women experiencing FGR. Following informed consent, 1560 women will be randomised to either immediate or delayed delivery. Women are being recruited from UK and European centres.

Potential participants are women with singleton non-anomalous pregnancies between 32+0 and 36+6 weeks of gestation in whom a SGA fetus is identified or one whose growth has slowed. This is defined as estimated fetal weight or abdominal circumference <10th percentile and/or having decreased by 50 percentiles since an ultrasound scan at 18–32 weeks. Biometry must have been performed in the 14 days prior to inclusion. Each centre will use local growth charts. Data is collected on absolute measurements and growth chart-derived percentiles. Once identified as potential participants women receive regular monitoring as per local standard of care for fetal condition, using ultrasound biometry, umbilical and MCA Doppler velocimetry assessments and cCTG (using Dawes-Redman criteria). This is recommended to be repeated every 14 days; these observational data are recorded.

Women become eligible for randomisation when signs of fetal cerebral blood flow redistribution are detected by Doppler, defined below and shown in the study flow chart (online supplemental file 1—flow chart).

10.1136/bmjopen-2021-055543.supp1Supplementary data

Delivery is based on UCR pulsatility index z-scores, of >1.5 (between 32+0 and 33+6 weeks) or >1.0 (34+0 to 36+6 weeks). These correspond to an absolute UCR of ≥1.0 at 32+0 to 33+6 weeks and ≥0.8 at 34+0 to 36+6 weeks. Abnormal UCR measurements must be repeated within 15 minutes–24 hours to confirm these values. This need not be consecutive, so that if the second measurement is normal the patient may still be randomised if a repeat Doppler measurement is abnormal within 72 hours of the first abnormal measurement. Randomisation will occur at the time of the second qualifying UCR measurement and is stratified by centre and gestational age. Randomisation is through the CASTOR website (Amsterdam, NL) into which eligibility, monitoring and outcome data are entered.

Women are consented in a two-stage process. Stage 1 (pre-eligible) consent is not a prerequisite and women may be consented directly for randomisation with stage 2 (eligible for randomisation) consent.

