#### Pre-eligible: consent for observational data collection

Consented for prospective data collection once identified as meeting criteria for SGA or slowed fetal growth (as defined above) but not meeting cerebral Doppler thresholds for randomisation or not willing to be randomised. This will include demographics, medical history, ultrasound findings and outcomes. This consent will include obtaining a personal email address, which is entered into and stored on Castor, and willingness to be contacted in the future for follow-up where women are randomised (online supplemental file 2—consent form for observational data collection).

10.1136/bmjopen-2021-055543.supp2Supplementary data

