#### Immediate delivery

Participants in the immediate delivery arm will be delivered by Caesarean or induction of labour will be commenced within 48 hours, allowing for administration of corticosteroids and infusion of magnesium sulphate as per local protocol and guidance. Start of induction of labour is defined as administering cervical preparation (cervical balloon, prostaglandins, etc), artificial rupture of membranes or administration of oxytocin.

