#### Delayed delivery

Participants in the delayed delivery arm will be monitored using twice weekly Doppler and cCTG monitoring, or more frequently based on local clinical protocols if required. Umbilical artery Doppler velocities may be measured in this time and delivery may be based on these safety net criteria (see box below). We strongly recommend that MCA measurements are not undertaken during monitoring in the delayed delivery arm. Delivery is indicated when short term variation (STV) is <4.5 ms on cCTG or there are repeated fetal heart rate decelerations. Once participants reach 37+0 weeks of gestation the delivery plan will be based on local protocols.

Box 1Delivery thresholds based on umbilical artery Doppler for participants in all arms of the studyUmbilical Doppler delivery thresholds.In all arms absolute indications for delivery include:Umbilical artery Doppler with reversed end diastolic flow after entry into the trial, ORUmbilical artery Doppler absent end diastolic flow from 34+0 weeks.

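### The pre-specified subgroup by corticosteroid administration is not limited to steroids given before randomisation, so its within-subgroup arm comparisons can be biased even with no treatment effect

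*Protocol article*

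**What the plan says.** The Main analysis section of the protocol article fixes the subgroup plan: "Additional pre-specified sub-group analyses will be carried out to analyse the primary outcome in the whole cohort". After the growth-percentile splits it names "maternal morbidity (yes/no) and corticosteroid administration (yes/no". Neither variable is tied to status at or before randomisation, and maternal morbidity is not defined.

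Four other statements bear on timing:

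- Study design: "Randomisation will occur at the time of the second qualifying UCR measurement".
- Immediate delivery: delivery or induction follows within 48 hours, "allowing for administration of corticosteroids and infusion of magnesium sulphate as per local protocol and guidance".
- Delayed delivery: women are monitored, with delivery on cardiotocograph or umbilical Doppler criteria. "Once participants reach 37+0 weeks of gestation the delivery plan will be based on local protocols". Corticosteroids are not mentioned for this arm.
- Main analysis: "All analyses will additionally adjust for gestational age at inclusion".

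The maternal secondary outcomes include gestational hypertension and pre-eclampsia, each specified as arising after study entry.

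**The concern.** A subgroup analysis keeps the protection of randomisation only if the subgrouping variable cannot be altered by allocation. Here allocation sets when delivery is planned, and with it the occasion for giving steroids. If women whose condition worsens are more likely to be treated, and worsening also predicts the primary outcome, the steroid-yes groups in the two arms have different mixes of prognosis. So do the steroid-no groups. The comparison within each can then depart from 1.00 when delivery timing has no effect at all.

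The trial is meant to inform delivery policy, and an apparent effect confined to steroid-treated or untreated pregnancies would be easy to believe. Maternal morbidity would share the problem only if it counts conditions arising after entry, since a longer pregnancy gives more time to develop them.

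**Working it through.** **The plan's own figures.** The design contrast is "from 15% in the delayed delivery to 9% in the immediate delivery". The odds ratio is (0.09/0.91)/(0.15/0.85) = 0.0989/0.1765 = 0.56, as stated. At two-sided 5% and 95% power, the two-proportion formula gives 760 per arm, or 793 with continuity correction. The stated 780 gives 95.5% power. Nothing here disputes the sample size.

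**Order of events.** Randomisation comes at the second qualifying Doppler measurement. The immediate arm's 48-hour window, with its allowance for steroids, follows. The delayed arm may run for weeks. Steroid administration can therefore come after allocation and depend on it.

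**Illustration 1: exact mixture, true odds ratio 1.00.** All inputs are assumed, except that the overall risk is set at 12%, the mean of 15% and 9%. Half the women are severe, with outcome risk r1; the rest have risk r0; both risks are the same in each arm. With s1 and s0 the probabilities of steroids in the two severity groups, the risk among treated women in an arm is

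(0.5·s1·r1 + 0.5·s0·r0) / (0.5·s1 + 0.5·s0).

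For untreated women, 1−s1 and 1−s0 replace s1 and s0.

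*Pattern A:* r1/r0 = 0.18/0.06; s1/s0 = 0.9/0.7 immediate, 0.7/0.2 delayed.
- Steroid yes: immediate (0.081+0.021)/0.80 = 0.1275; delayed (0.063+0.006)/0.45 = 0.1533; odds ratio 0.81.
- Steroid no: immediate (0.009+0.009)/0.20 = 0.0900; delayed (0.027+0.024)/0.55 = 0.0927; odds ratio 0.97.

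*Pattern B:* same risks; 0.95/0.5 immediate, 0.6/0.3 delayed.
- Steroid yes: 0.1386 against 0.1400; odds ratio 0.99.
- Steroid no: 0.0709 against 0.1036; odds ratio 0.66.

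*Pattern A with weaker prognosis* (0.15/0.09): odds ratios 0.89 (yes) and 0.99 (no).

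*Controls:* if steroid probabilities do not differ by arm, both odds ratios are 1.00. If they differ but severity does not predict the outcome (r1 = r0 = 0.12), both are again 1.00. Bias needs both conditions.

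*Maternal morbidity counted after entry:* pattern A risks with probabilities 0.30/0.10 immediate and 0.50/0.20 delayed give 1.03 (yes) and 1.07 (no). With risks 0.15/0.09 they are 1.02 and 1.03.

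**Illustration 2: does the planned adjustment help?** This is a simulation with no treatment effect. Assumptions: 85% steroid use if delivered before 35+0 weeks and 10% otherwise; median delay 14 days; a latent severity that raises both the speed of deterioration and the outcome risk by 0.4, 0.7 or 1.0 log-units per SD. Steroid use was 54% (immediate) and 28–29% (delayed), and the overall odds ratio 0.99–1.00. The adjusted columns come from a rebuild that adds entry uniform over 32–37 weeks and outcome log-odds falling 0.3 per week; its crude steroid-no values were 0.86, 0.92 and 1.00.

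| Severity | Yes, crude | No, crude | Yes, adjusted | No, adjusted (two strata) | No, adjusted (continuous) |
|---|---|---|---|---|---|
| 0.4 | 0.92 | 0.85 | 0.93 | 0.98 | 1.03 |
| 0.7 | 0.81 | 0.91 | 0.84 | 1.02 | 1.07 |
| 1.0 | 0.73 | 0.99 | 0.74 | 1.08 | 1.13 |

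Adjustment takes out much of the departure among untreated women at the weakest severity link. It leaves the steroid-yes odds ratios almost where they were, because deterioration after entry is not a function of gestational age at inclusion.

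**The case against.** Several points against stand.

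- The delayed-arm text is silent on steroids, so treatment there mainly on early deterioration is plausible but not documented. Nor does anything rule out a course before randomisation; up to 72 hours may separate the qualifying measurements.
- The odds ratios rest on assumed inputs. Part of the crude steroid-no departure is confounding by gestational age, which the plan already adjusts for.
- Any bias may be small beside the sampling error. With 54% and 28.5% of 780 treated (421 and 222) and 12% risk, the variance of the log odds ratio among treated women is 1/(421×0.12×0.88) + 1/(222×0.12×0.88) = 0.065. The standard error is 0.26 and the 95% interval factor exp(1.96×0.255) = 1.65. The interaction standard error is about 0.33, so the crude pairs above correspond to z of +0.24, −0.35 and −0.93. A spurious finding is possible, not shown to be likely.
- An analysis plan not shown could set the timing.

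None of this removes the core point. The article lists the subgroup as pre-specified, and followed as written it conditions on something allocation can change.

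A reader might infer that the maternal morbidity subgroup is equally affected. The documents do not support that. The article says so explicitly when it means conditions arising after entry, and the observational data collection covers medical history ("This will include demographics, medical history, ultrasound findings and outcomes"), so baseline status is at least as natural a reading.

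**Conclusion.** The point holds for corticosteroids: as written, the split is not a randomised comparison, and its within-subgroup effects can be biased under a null treatment effect. A reader might go further and say that they are biased. That needs both an effect of allocation on steroid use and a prognostic cause shared with the outcome, and the article gives no rates by arm from which to establish either. Size and direction are therefore unknown. The mixture range of 0.66 to 0.99 shows only what assumed inputs can produce without gestational-age adjustment.

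For maternal morbidity the point is conditional on counting conditions that arise after entry, and the illustrated effect is small (1.02 to 1.07). It would also be wrong to infer that the trial's main result is in doubt. The fault is confined to secondary subgroup analyses and is worth correcting before the analysis plan is finalised.

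**What to change.** In the Main analysis section, and in the analysis plan, choose one of two wordings for corticosteroids:

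1. Define the subgroup by a steroid course given before randomisation.
2. If steroids received at any time are used, present the results descriptively, with no test and no causal reading of the intervention effect. The article already takes this approach, if numbers allow, for its three-way growth-percentile split.

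In the same sentence, state that maternal morbidity means morbidity present at randomisation.

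The change needs no extra participants. Under the first option fewer women count as steroid-exposed, so that subgroup is less precise. The article does not say that steroid dates are recorded, and it describes medical history under a consent stage that is optional. Both data items should be checked for all randomised women before the first option is adopted. Adding a subgroup by gestational-age stratum would be reasonable, but it is a preference and not needed to correct this point.
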